**Technological, feasibility, and acceptability measures**			
	Survey of acceptability	This measure, adapted from CyberSenga [82] (a mobile health HIV study with youths in Uganda), is a 12-item survey with a Likert scale of 1 to 3 (disagree, somewhat agree, and strongly agree).	Immediately after the intervention
	Number of messages viewed	Retrieved via user database consistent with previous m4RH evaluations [54]	Continuous
	Type of messages (regarding sexual health, mental health, and alcohol use)	Retrieved via user database consistent with previous m4RH evaluations [54]	Continuous
	Mental health and alcohol use screens completed (AUDIT, GAD-7, and PHQ-9)	Retrieved via user database	Continuous
	HIV clinic locator (number of times used)	Retrieved via user database	Continuous
	Feasibility	Enrollment of recruited adolescents	Immediately after the intervention

^a^CASPE: COVID-19 Adolescent Symptom & Psychological Experience Questionnaire.

^b^PrEP: pre-exposure prophylaxis.

^c^PHQ-9: 9-item Patient Health Questionnaire.

^d^AUDIT-C: Alcohol Use Disorders Identification Test–Consumption.

^e^GAD-7: 7-item Generalized Anxiety Disorder Questionnaire.

Similarly, the GAD-7 [71] will be used to screen and measure the severity of generalized anxiety symptoms among participants. Through Kirabo, we will administer the first 2 questions of the GAD-7. Table 2 provides additional information regarding this measure. To be cautious and consistent with StrongMinds’ approach, we will use a cutoff point of 8 to determine a referral to a StrongMinds counselor.

The 3-item Alcohol Use Disorders Identification Test–Consumption (AUDIT-C) [80] will be used to measure hazardous alcohol use (Table 2). Similar brief measures have been used and validated globally, specifically in East Africa and Uganda [18,83-89]. To improve user experience and consistent with the prior work described subsequently, screener length will be determined by an adolescent’s response to initial questions. Table 2 provides additional details regarding the AUDIT-C [90].

In our initial version of Kirabo, if an adolescent screened positive for symptoms of depression, anxiety, or hazardous alcohol use, the adolescent was provided with the contact number of our mental health partner StrongMinds.

### Phases 3 and 4: Administration of Pretest and Production

The ICHAD has research relationships with 70 secondary schools in the region, and a well-established protocol for recruitment is described subsequently. The field research team (RK, OIN, and PN) worked primarily out of the ICHAD offices in Masaka, Uganda. ICHAD researchers distributed flyers to students and staff, noting that adolescents aged 15 to 19 years may be eligible to participate. Research team members with no relationship with students conducted the recruitment. Further, students did not receive any class credit or extra credit for participating. Students were compensated for their time at rates consistent with the ICHAD policies and in accordance with Ugandan and US ethics board guidance. Adolescents were compensated 8500 Uganda shillings (US $2.25) for participating in the mobile phone–based portion of the research, and adolescents who joined the focus groups were offered an additional 20,000 Uganda shillings (US $5.30). Teachers were not informed about which students were contacted and consented/assented to participate. We will use similar procedures to recruit for the RCT described subsequently. That said, if the current COVID-19 protocols or other factors result in the school not currently being in session, a head teacher may provide researchers with a list of students who have expressed interest and meet the age eligibility for a final screen by the research team.

To conduct the pretest, we recruited 24 adolescents (aged 15 to 19 years) from 2 secondary schools in southern Uganda. Over a 1-week period, the adolescents were prompted via a daily automated SMS text message, amounting to 5 prompts per week, to interact with Kirabo. We tested the following three different methods of contacting Kirabo: (1) through IVR by dialing 161, (2) through unstructured supplementary service data (USSD) by dialing *161#, or (3) through SMS text messaging by texting “Hi” to 161. IVR allows callers to access prerecorded messages through speech recognition. USSD is similar to SMS text messaging, except that the messages disappear after a texting session. Only adolescents with phone numbers registered in our study could access the messages.

The GAD-7 scores ranged from 0 to 15 (mean 4.39, SD 3.77), and of the 24 participants, 5 (21%) scored ≥10 and thus screened positive for clinically significant symptoms of anxiety. In total, 3 (12%) adolescents screened positive for both symptoms of anxiety and depression. No adolescents screened positive on the AUDIT scale, with scores ranging from 0 to 4 (mean 0.5, SD 1.01).

In focus groups with 19 (79%) of the 24 adolescents, 10 (53%) preferred SMS text messaging and 9 (47%) preferred USSD, noting that SMS text messages arrived more quickly and could be revisited because they were saved on the phone. A female student aged 15 years said, “if the messages are saved, it can help me to seek clarification of what I haven’t understood. I can review those messages for me to understand them well.” None of the adolescents preferred IVR, which had the most reported issues. The adolescents explained that IVR calls frequently dropped mid-call owing to poor phone service. This would require an adolescent to call back and start at the beginning of the menus. Not surprisingly, the adolescents expressed frustration when describing this process. In addition, although using IVR was free, some adolescents assumed that calling the IVR system would cost them money. Furthermore, adolescents were hesitant to call StrongMinds counselors because they did not want to incur charges. Some adolescents noted that receiving messages after chores in the morning was preferable, whereas the majority preferred to receive messages after school and in the evening.

With regard to HIV prevention, most adolescents reflected that Kirabo helped them learn about PrEP and the health centers where they could access HIV services. As one of the adolescents succinctly explained, “it [Kirabo] is good because most of us have not been knowing what PrEP is.” Another adolescent added, “the messages I liked most were those regarding PrEP. I got more clarification about PrEP because I only knew about a tablet that you take to prevent yourself from getting infected with HIV, but I didn’t know its name.” A third adolescent described how Kirabo “directed us to the nearest health facilities where a person can easily access HIV testing and PrEP services.” These excerpts and the broader focus group discussions align with prior work showing an unmet need for mobile health HIV prevention interventions for adolescents in the region [23].

### Phases 5 to 6: Consultation With Topical Experts and Integration

In addition to weekly meetings where author 1 discussed and designed the intervention and modifications with coauthors 2, 3, and 4, the first iteration of Kirabo was presented to a group of topical experts as part of an HIV Implementation Science and Inter-Centers for AIDS Research (CFAR) Fellowship program (2022-2023; P30AI094189). In the culminating session of this 9-month training program, author 1 presented pretest findings to 30 trainees (graduate students, postdoctoral fellows, and early career faculty) and 5 faculty mentors in person (Drs [name], [name], [name], and [name]). This presentation was given in Baltimore, Maryland, on April 5, 2022. One of the audience members suggested that given the potentially sensitive nature of the messages, we should send a preliminary greeting message with no sexual or mental health content. Another point of discussion was to consider using a shorter follow-up period of 3months as opposed to the initially planned 6 months. Comments on the presentation in combination with our pretest findings led us to make the following three key changes to Kirabo in the proposed RCT:

Most adolescents preferred SMS text messaging. Thus, to streamline our delivery, recruitment, and evaluation, we decided to focus on SMS text messaging in this pilot RCT. In addition, to protect privacy, we added an initial message to be sent on each day of the intervention period that asked, “is this a good time to chat?” By contrast, the initial prompt from the pilot test immediately introduced the topic of the day (HIV testing, mood, etc). If adolescents respond with “yes,” then they would be sent the follow-up message that introduces the topic of the week. If adolescents respond with “no,” they would be sent a message that says, “ok thanks, write back with yes when you are free and available.”In the pretest, adolescents who screened positive for symptoms of depression, anxiety, or hazardous alcohol were provided with the contact number of the general StrongMinds counselor. As described earlier, adolescents expressed concern that they would incur charges by calling StrongMinds counselors. Therefore, we revised our methods (including language in our consent forms), and in the RCT, we will provide a daily update to StrongMinds counselors with a list of contact numbers of adolescents who screened positive for symptoms of depression, anxiety, or hazardous alcohol use.On the basis of our initial focus group discussions and our presentation at the HIV Implementation Science Fellowship, we expect that a 3-month follow-up will be sufficient to determine feasibility and accessibility. In addition, a shorter follow-up period will limit the possibility of unforeseen historical or COVID-19–related interruptions.

### Phases 7 to 8: Training and RCT Pilot Study

#### Procedures

We plan to conduct a 2-arm, randomized controlled study via mobile phones among adolescents in the greater Masaka region of Uganda. We will compare Kirabo to an inactive control and evaluate whether adolescents who interacted with Kirabo had higher rates of self-reported HIV testing (yes/no; verified with the HIV clinic when possible) immediately after the intervention and at the 3-month follow-up assessment. Secondary outcomes include differences in condom use, PrEP knowledge, PrEP uptake for eligible patients, HIV-related knowledge and sexual risk behaviors, and antiretroviral treatment uptake for eligible patients. Exploratory aims include the number of participants who screen positive for symptoms of depression, anxiety, and hazardous alcohol use and the proportion of confirmed linkages to mental health counseling.

Adolescents (aged 15-19 years) in the greater Masaka region in southern Uganda who own a mobile phone will be eligible for the trial. Adolescents will be involved in the trial for approximately 5 weeks with a 3-month follow-up assessment (Figure 2). After informed assent and parental permission, the baseline assessment, and confirmation of eligibility, adolescents will be randomly assigned to the Kirabo intervention group or standard of care group. Randomization will be performed in a 1:1 ratio and stratified by gender and school (to minimize contamination) with a block size of 10. We anticipate recruiting students from 20 schools. The treatment assignments will be generated using a pseudorandom number generator. An electronic list of IDs, access codes, and credentials will be provided securely to the sites.

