**Methods:**

We identified Mobile 4 Reproductive Health for adaptation using the assessment, decision, administration, production, topical experts, integration, training, testing (ADAPT-ITT) framework. Mobile 4 Reproductive Health is an evidence-based automated 2-way SMS text messaging and interactive voice response platform that offers sexual and reproductive health information and links users to HIV clinics in East Africa. Through ADAPT-ITT we refined our approach and created Kirabo, an SMS text message–based intervention for linking adolescents and young adults to health services, including HIV testing and mental health counseling. We will conduct a 2-arm randomized controlled trial in Masaka, Uganda. Adolescents (N=200) will be recruited from local schools. Baseline sociodemographic characteristics, HIV test history, and behavioral health symptoms will be assessed. We will evaluate acceptability and feasibility using surveys, interviews, and mobile phone data. The preliminary efficacy of Kirabo in increasing HIV testing and linking users to mental health counselors will be evaluated immediately after the intervention and at the 3-month follow-up. We will also assess the intervention’s impact on self-efficacy in testing for HIV, adopting PrEP, and contacting a mental health counselor.

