#### Three Main Modifications

In Kirabo, we made the following three main modifications to the existing m4RH approach:

In prior work, m4RH was disseminated via radio and magazine advertisements and at family planning clinics [52,53,55,65]. To ensure that we reach the target population of adolescents for Kirabo, we partnered with local schools and will disseminate Kirabo at the schools or via SMS text messages. Our researchers will deliver an IMB-informed oral script, describing Kirabo in person at local schools and further disseminating Kirabo via flyers.When m4RH was designed, PrEP was not available in sub-Saharan Africa. Thus, in Kirabo, we added and updated the existing m4RH HIV prevention menu to include the current information on PrEP and the location of local clinics. To create PrEP messages, we used text from the Centers for Disease Control and Prevention’s (CDC) informational materials and published qualitative research studies [66-68]. Figure 1 displays an example of PrEP messages from Kirabo, with the numbers indicating user responses and menu selections. In Figure 1, Kirabo asks the adolescent the following question: “have you heard of PrEP? Reply 1 for Yes, 2 for No.” The adolescent then replies “2,” indicating that they had not previously heard of PrEP and thus triggering Kirabo to begin to describe PrEP. Furthermore, we added additional details, such as local landmarks, directions, and contact numbers for local HIV clinics. As part of this formative work, we contacted 6 HIV clinics in the southern Ugandan region. Of the 6 clinics, 5 confirmed that they were currently able to prescribe PrEP to adolescents according to the national guidelines and had ample PrEP medication in supply [69]. The clinic location and contact information were included in the adapted intervention.Finally, because we know that mental health is critical to HIV prevention efforts, in Kirabo, we additionally focus on behavioral health. Adolescents will complete screeners, which are then used to tailor the SMS text messages they receive.

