**Behavioral, mental health, and alcohol use measures**			
	Demographics	Items developed for previous Suubi studies [72-74], including age, sex, parents’ occupation, household size, orphanhood status, primary caregiver, and community of origin	Baseline
	COVID-19 experiences	CASPE^a^ (adapted from Suubi+Adherence [74] and the study by Ladouceur [75])	Baseline
	HIV testing	Self-report of HIV test (yes/no; past year [at baseline], during the study period [immediately after the intervention], and past 3 months [at follow-up]) confirmed with proof of results from the clinic using measures and procedures adapted from Suubi studies [72-74]	Baseline, immediately after the intervention, and 3-month follow-up
	Intention to test for HIV	Questions adapted from a study of secondary school students in Uganda [76]	Baseline, immediately after the intervention, and 3-month follow-up
	Self-efficacy	Questions adapted from a study with secondary school students in Uganda [76] and a study with high school students in the United States [77], including questions regarding self-efficacy in testing for HIV, trying PrEP^b^, using condoms consistently, contacting a behavioral health counselor	Baseline, immediately after the intervention, and 3-month follow-up
	Current HIV prevention strategies	This measure includes items developed for previous Suubi studies [72,73] in Uganda (in addition to a question regarding PrEP; range 5-25; 5 question items; α=.70), for example, “I think it is very important to use condoms every time one has sex,” “as a teenager I think AIDS is a threat to my health,” and “I think all people my age who have sex should use condoms.” Scores range from 4: strongly agree; 3: somewhat agree; 2: somewhat disagree; to 1: strongly disagree.	Baseline, immediately after the intervention, and 3-month follow-up
	HIV-related knowledge	This measure includes items from previous Suubi studies [72,73] in Uganda; this measure includes 13 items about HIV infection and prevention mechanisms (range 0-16; 16 question items; α=.83), for example, “HIV can be passed by an infected person even though that person is not feeling sick.” Possible scores are 1: true; 2: false; and 3: don't know or 1: not sure; 2: unsafe; and 3: safe.	Baseline, immediately after the intervention, and 3-month follow-up

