	Sexual risk behaviors	This measure includes items from previous Suubi studies [72,73] in Uganda (range: 5-25; 5 question items; α=.76), for example, “I believe it’s OK to have sex without protection with someone you know.” Scores range from 1: never; 2: sometimes; 3: about half of the time; 4: most of the time; to 5: always.	Baseline, immediately after the intervention, and 3-month follow-up
	PrEP knowledge	Adapted 13-item true-false questionnaire on PrEP knowledge [78,79] including questions such as “PrEP is a pill you can take to prevent HIV” and “PrEP is only for people who are HIV negative”	Baseline, immediately after the intervention, and 3-month follow-up
	Depressive symptomatology	PHQ-9^c^ [70], a standardized 9-item self-report instrument used to assess depression, is used. Participants rate the frequency of their symptoms over the past 2 weeks. Items are rated on a 4-point scale, ranging from 0 (not at all) to 3 (nearly every day), and scale scores range from 0 to 27. PHQ-9 scores of 5 to 9 represent minimal to mild depression and 10 to 20 represent moderate to severe depression. A score ≥10 has a sensitivity of 88% and a specificity of 88% for major depression.	Baseline and immediately after the intervention
	Anxiety	GAD-7^d^ [71], is a standardized instrument that asks participants to rate their symptoms over the past 2 weeks on a 4-point scale ranging from 0 (not at all) to 3 (nearly every day), is used. Overall scores for the GAD-7 range from 0 to 21. At a cutoff point of 10 (indicative of clinically significant symptoms), the sensitivity and specificity of the scale equal 89% and 82%, respectively. The GAD-7 has a Cronbach α of.92, indicating good internal consistency, and an intraclass correlation of 0.83, indicating good procedural validity.	Baseline and immediately after the intervention
	Alcohol use disorder screen	AUDIT-C^e^ [80,81], a 3-item screener excerpted from the full standardized 10-item AUDIT tool for assessing hazardous alcohol consumption, is used. Items are scored on a 5-point scale for a possible score of 0 to 12. The higher the score, the higher the risk of hazardous alcohol consumption. AUDIT-C scores of ≥4 in men and ≥3 in women are considered positive for hazardous alcohol consumption.	Baseline and immediately after the intervention
	Reported (and confirmed) sessions with mental health counselor	Self-report and local school and clinic records	Baseline and immediately after the intervention

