### Measures

#### Overview

To evaluate the intervention’s impact, there will be 3 main assessment time points: baseline, immediately after the intervention, and 3-month follow-up. Table 2 provides a full list of measures. The primary outcome will be self-reported HIV testing, confirmed by HIV clinic records when possible. We will also measure the uptake of HIV prevention strategies (PrEP uptake and condom use) and, although we expect this to be a rare occurrence, the initiation of antiretroviral treatment. For adolescents who screen positive for behavioral health problems, we will confirm self-reports of linking to mental health care with a StrongMinds counselor.

Many of the measures have already been used, pretested, and made culturally appropriate to the Ugandan context in past studies [92,93], including current HIV prevention strategies and HIV-related knowledge. New measures, such as PrEP knowledge, will be adjusted according to the established ICHAD procedures. Specifically, to assess the uptake of HIV prevention strategies, we will compare presurvey and postsurvey scores from the current HIV prevention strategy measures that have been previously used in this region of Uganda with adolescents (Table 2) [72,73]. For questions measuring sensitive behaviors (ie, sexual risks), we will use audio computer-assisted self-interviews so that the participants may take the survey themselves on a minilaptop.

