### Statistical Analysis

#### Primary and Secondary Outcomes and Analysis

Summary statistics will be used to describe all metrics and compare them between the students receiving Kirabo and those in usual care at baseline, 1-month postintervention assessment, and the final 3-month follow-up assessment. Means and SDs will be used for continuous outcomes, followed by box plots, and frequency tables will be used for binary and categorical metrics. The primary analysis of this RCT will test whether postintervention HIV testing rates among the adolescents who interacted with Kirabo are significantly higher than those who received standard of care. We will use a generalized linear mixed model to determine statistical significance. In the model, the outcome is the binary indicator of whether an adolescent received an HIV test during or immediately after the intervention. We will also examine the differences between the model at the 3-month follow-up. The main predictor is the intervention assignment (Kirabo or usual care). The school will be included in the model as the random effect to adjust for within-school correlations. We will apply similar analyses to investigate the impact of Kirabo on the secondary outcomes.

Depending on the nature of the outcome, we will use different link functions in the generalized linear mixed model. We will use the identity link for continuous outcomes, the logistic link for binary outcomes, and the log function for ordinal outcomes. For incidence/frequency outcomes, a log function with adjustment for exposure time will be used. We will formally test whether the students in the 2 intervention groups have comparable baseline characteristics, including demographic factors, moderators, and variables measuring potential mechanisms of action (Table 2). If any of these variables are significantly different at baseline, they will be included in the model to adjust for their potential confounding effects.

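### PrEP and antiretroviral uptake are stated both with and without a restriction to eligible patients; to the extent eligibility rests on testing after randomization, an arm comparison within that subset is not protected by randomization

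*Protocol article*

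**What the plan says.** All references are to the protocol article.

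- **Outcome list (Phases 7 to 8, Procedures).** The secondary outcomes are differences between arms and include "PrEP uptake for eligible patients, HIV-related knowledge and sexual risk behaviors, and antiretroviral treatment uptake for eligible patients". The article does not say how or when eligibility is judged.
- **Second statement (Measures, Overview).** The same two uptake outcomes appear with no eligible subset. Antiretroviral initiation is expected to be rare. Uptake of prevention strategies is to be assessed from survey scores before and after the intervention.
- **Primary outcome (Measures, Overview).** "The primary outcome will be self-reported HIV testing, confirmed by HIV clinic records when possible".
- **Analysis (Primary and Secondary Outcomes and Analysis).** The primary model is a generalized linear mixed model with assigned arm as main predictor. Then: "We will apply similar analyses to investigate the impact of Kirabo on the secondary outcomes". Intention to treat is stated for the primary aim (Handling of Missing Data).
- **Entry and baseline.** Adolescents of the stated age and region "who own a mobile phone will be eligible for the trial". On baseline data the abstract says: "Baseline sociodemographic characteristics, HIV test history, and behavioral health symptoms will be assessed". In Table 2 the HIV testing item at baseline is a report on the past year.
- **What bears on eligibility.** Local clinics were "currently able to prescribe PrEP to adolescents according to the national guidelines" (Three Main Modifications); the criteria are not given. One item of the PrEP knowledge questionnaire in Table 2 reads "PrEP is only for people who are HIV negative".

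**The concern.** A randomized comparison is safe in a subset only if the arm cannot influence who belongs to it. Kirabo is meant to work in sequence: information, then a clinic visit and an HIV test, then PrEP or treatment. If a participant counts as eligible once HIV status is known, and that status is learned from a test taken during the trial, then Kirabo changes the denominator. The eligible group in the Kirabo arm would contain adolescents who tested because of Kirabo, and their counterparts in the control arm would be left out.

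Two things then go wrong. The gain made through testing cancels out of the rate. And the two eligible groups differ in kind, because those who test when prompted need not resemble those who would test anyway. The direction of the resulting bias is not known in advance.

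The Limitations section says the pilot's preliminary data will feed a larger trial. A PrEP signal that is masked or distorted here would carry into that design.

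**Working it through.** **1. The article's own figure.** Effectiveness Power Analysis: 100 per arm, 26% against 46%, significance level .05, power 80%. Two-sided pooled z test with continuity correction:

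- Mean rate = (0.26 + 0.46)/2 = 0.36.
- Standard error under the null = √(0.36 × 0.64 × 2/100) = 0.0679.
- Standard error under the alternative = √((0.26 × 0.74 + 0.46 × 0.54)/100) = 0.0664.
- Power = Φ((0.20 − 0.01 − 1.96 × 0.0679)/0.0664) = Φ(0.86) = 80.5%.

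The 80% reproduces (without the correction it is 84.3%). The article gives no figure for PrEP or antiretroviral uptake, so the start rates below are assumptions.

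**2. Is the subset fixed before randomization?** Entry depends on age, region and phone ownership. Baseline records a self-reported test history. No study test is described. Nothing in the article ties eligibility to baseline data, so membership can depend on what happens after randomization.

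**3. Equal start rates.** Suppose eligibility requires a test in the trial, every tester counts as eligible, and the start rate among testers is q in both arms. Starts per 100 randomized = 100 × testing rate × q.

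| q (assumed) | Control, of 100 | Kirabo, of 100 | Ratio | Among testers |
|---|---|---|---|---|
| 10% | 2.6 | 4.6 | 1.77 | 10% vs 10% |
| 20% | 5.2 | 9.2 | 1.77 | 20% vs 20% |
| 30% | 7.8 | 13.8 | 1.77 | 30% vs 30% |
| 50% | 13.0 | 23.0 | 1.77 | 50% vs 50% |

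The ratio is 0.46/0.26 = 1.77 whatever q is. The denominators among testers are 26 and 46.

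**4. Unequal start rates.** Split the Kirabo testers into the 26% who would test anyway (start rate a) and the extra 20% (start rate b). Among testers: control = a, Kirabo = (0.26a + 0.20b)/0.46. Over all randomized: control = 0.26a, Kirabo = 0.26a + 0.20b.

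- a = 30%, b = 10%: among testers 30% vs 0.098/0.46 = 21.3%, a difference of −8.7 points. Over all randomized 7.8% vs 9.8%, a difference of +2.0 points. The sign reverses.
- a = 20%, b = 40%: among testers 20% vs 0.132/0.46 = 28.7%, a difference of +8.7 points. Over all randomized 5.2% vs 13.2%, a difference of +8.0 points. The +8.7 comes wholly from the change in who tested, since those who would test anyway start at 20% in both arms. As a ratio, the comparison among testers (1.43) is smaller than over all randomized (2.54).

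**5. Status partly known at baseline.** Suppose the 26% with a past-year test count as known in both arms, and the other 74% test in the trial at 26% or 46%. Known status is then 26 + 74 × 0.26 = 45.2 vs 26 + 74 × 0.46 = 60.0 per 100, a ratio of 1.33. At q = 20% this gives 9.0 vs 12.0 starts per 100 randomized, still 20% vs 20% within the subset. The distortion shrinks but does not vanish.

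**6. Antiretroviral treatment.** At an assumed HIV prevalence of 1% to 5%, testers found positive number 26 × 0.01 to 26 × 0.05 = 0.3 to 1.3 in control and 46 × 0.01 to 46 × 0.05 = 0.5 to 2.3 under Kirabo. Over all randomized, 1 to 5 per arm would be positive. Neither denominator supports a comparison.

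**The case against.** The strongest reply is that the article never says eligibility comes from a test during the trial. The term is undefined, the prescribing criteria sit in national guidelines that are not shown, and the one link to HIV-negative status is an item in a knowledge questionnaire printed without an answer key. Eligibility could rest on baseline test history or baseline sexual risk behavior, and a full protocol or SAP may say so. This stands. A reader might infer that the eligible group exists only after an HIV test; the documents do not support that. Some participants may know their status at entry, and about 26% are expected to have tested in the preceding year.

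A reader might also infer that uptake will be compared only among the eligible. The Overview under Measures speaks against this, since it gives the same outcomes without restriction, and the analysis section names no subset.

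The size can be challenged too. Kirabo also delivers PrEP information, so start rates among testers may differ by arm and the exact cancellation would not occur. The 26% is a 12-month rate set against a 5-week intervention. Both points stand, which is why step 4 varies the rates and the figures serve only as illustration.

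The reply does not remove the point. It is not that a definition is missing. The outcome list states a denominator that nothing in the article fixes before randomization, and another section states a different one. A behavioral definition would not by itself be safe either: sexual risk behavior is also a secondary outcome and is measured again after baseline.

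**Conclusion.** The point holds in a conditional form. Procedures and the Overview under Measures disagree on the denominator for PrEP and antiretroviral uptake. To the extent that eligibility depends on HIV status learned after randomization, an arm comparison within the eligible subset can hide, reverse or exaggerate an effect that works through testing.

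The size depends on assumptions. With the article's testing rates and equal start rates among testers, a ratio of 1.77 over all randomized becomes 1.00 within the subset. If past-year testers already count as known at baseline, a ratio of 1.33 becomes 1.00. With unequal start rates the sign can reverse (+2.0 points against −8.7). A control testing rate for a shorter window would be lower and the tester subset smaller.

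The point rests mainly on PrEP. For antiretroviral treatment the limit is rarity, which the article concedes. It would go too far to say that the trial's objective is answered wrongly: these are two of several secondary outcomes of a pilot whose main purpose is acceptability and feasibility, and the primary analysis of HIV testing is unaffected.

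**What to change.** Reconcile Procedures with the Overview under Measures, as follows.

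- **PrEP uptake:** a yes/no outcome over all randomized participants, compared by assigned arm. A participant with follow-up who was not tested counts as not started; missing follow-up is handled under the article's missing-data rule.
- **Cascade:** tested, eligible and started as counts per arm, descriptive only.
- **Eligible subset:** compare arms within it only if it is defined from data recorded before randomization.
- **Antiretroviral starts:** counts per arm over all randomized, without a test.

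This takes a few sentences in the outcome definitions and no added visits or tests. It does need a yes/no answer on PrEP; Table 2 mentions a PrEP question without showing its wording, and the restricted outcome would need the same answer. The downside is smaller absolute rates. At 5.2% vs 9.2% with 100 per arm, a two-sided 5% test without continuity correction has about 19% power, so the result should be read as an estimate with its confidence interval.
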